##### Follow-Up Assessment (T1)

At T1, some global data, regarding participant's social inclusion, autonomy and psychiatry follow-up between T0 and T1, will be collected in a general database. Social adaptation and interpersonal relationship will be reassessed, using the SASS (36, 37).

The perception of therapeutic alliance will be tested by the child version of the Helping Alliance Questionnaire for Child and Parents (HAQ-CP) (50, 51), a 15-item self-report questionnaire on a six-point scale (1–6), including two sets of items: a 13-item therapeutic alliance subscale and a two-item overall psychological state subscale. The overall score for the therapeutic alliance ranges from 13 to 78 with higher scores representing higher levels of therapeutic alliance.

### Descriptive Statistics

With regard to categorical sociodemographic variables, summary tabulations of absolute and relative frequencies in each category of qualitative variables will be presented. Missing data will be treated, in the first instance, with pairwise deletion. After data collection, in case that missing completely at random data are believed to be predominant, we will proceed to listwise deletion. If missing at random data are more plausible, regression imputation will be used.

With regard to continuous sociodemographic variables, the number of participants, mean, median, standard deviation, minimum and maximum values, and interquartile ranges will be presented. Mean and standard deviation will be used as central tendency and dispersion indicators when the distribution is approximately normal, with medians and interquartile ranges used otherwise. The normality of the distributions will be assessed with graphical displays (histogram, box plot and normal plot).

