**Figure 2 F2:**
[figure not shown]
Conceptual model of the primary aim.

Regarding our primary objective, two kind of analysis will be conducted: Pearson correlation and mediation. We computed an *a priori* power analysis using G^*^Power software to estimate the sample size for these tests. To reach a medium effect size (i.e., r = 0.3), with an α-error of 5% (two-sided) and a β-error of 80%, the total sample size represents 84 participants for Pearson correlations and 149 participants for mediation analysis (based on a three groups IV and one mediator). We decided to recruit 300 youth in our study to allow for up to half of the participants dropping out of the study.

To reach our secondary objective, we will first identify the most powerful predictors between risk and protective factors with linear regression analysis. Then, to assess the weight of each risk and protective factor identified with linear regression in the relation between the difference of HONOSCA-SR scores and WHOQOL-BREF scores between T0 and T1, mediation/moderation analyses will be conducted using the PROCESS macro in SPSS (52).

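### In the missing-at-random branch, regression imputation of T1 outcomes without carrying imputation uncertainty would understate standard errors and inflate type I error

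*Protocol article*

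**What the plan says.** The missing-data rule stands under Descriptive Statistics and has three parts. The default is deletion: "Missing data will be treated, in the first instance, with pairwise deletion". After data collection, listwise deletion follows if data missing completely at random are thought to predominate. Otherwise, "If missing at random data are more plausible, regression imputation will be used". No residual draw, multiple imputation or variance correction is mentioned, and no other missing-data rule appears in the article.

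Data Analysis and Sample Size makes the T0-T1 changes in HONOSCA-SR and WHOQOL-BREF the dependent variables and names Pearson correlation and mediation as the primary analyses. On attrition it says: "We decided to recruit 300 youth in our study to allow for up to half of the participants dropping out of the study". The Attrition Bias section cites retention above 70% in similar populations.

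**The concern.** In its ordinary meaning, regression imputation replaces a missing value with the fitted value from a regression. The filled-in points lie on the regression line, without scatter, and are then counted as real observations. Residual variance is too small and the apparent sample size too large, so standard errors, intervals and p-values are too favourable. Pearson's r rises as well, because the outcome's variance shrinks while its covariance with the predictor does not.

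This touches the primary objective, since anyone lost before T1 has no change score. Missing at random is also a realistic branch: the Introduction describes young people leaving care at this age, so dropout unrelated to clinical state is doubtful. The fault therefore lies in the branch most likely to matter.

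**Working it through.** **Inputs from the article (Data Analysis and Sample Size; Attrition Bias).** Two-sided alpha 5%; r = 0.3; 84 participants for correlation and 149 for mediation; 300 recruited; dropout up to 50%; cited retention above 70%, so dropout below 30%.

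**Assumed.** T0-T1 correlation of the outcome: 0.3, 0.5 and 0.7.

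**The plan's own figures.** Simulating the exact correlation test gives power 0.801 at n = 84 and 0.795 at n = 83, so 84 reproduces. This requires reading "a β-error of 80" per cent as power of 80%. The 149 reproduces under an inferred set-up: multiple regression, f² = 0.09, five tested predictors, 80% power. Then 149 / (1 − 0.5) = 298, close to 300.

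**Formula, simplest case.** Let a share d of outcomes be imputed without a residual from the exposure alone.
- The slope equals the complete-case slope, with true variance σ² / [n(1−d)·s²], where s² is the exposure variance.
- The residual sum of squares is that of the n(1−d) observed cases but is divided by about n, so the reported variance is σ²(1−d) / (n·s²).
- Reported SE / true SE = √[(1−d)²] = 1 − d.
- Type I error = 2 × [1 − Φ(1.96(1−d))].
- d = 0.5: ratio 0.50, error 2 × [1 − Φ(0.98)] = 32.7%.
- d = 0.3: ratio 0.70, error 2 × [1 − Φ(1.372)] = 17.0%.

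The test of Pearson's r is the test of this slope, so the result carries over.

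**Simulation.** N = 300, no true exposure effect. Where three values are given, they are for T0-T1 correlations of 0.3 / 0.5 / 0.7, with the change score as outcome and T1 imputed from T0 and the exposure.

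| Dropout | Method | Reported SE / true SE | Type I error |
|---|---|---|---|
| 50% | No residual, exposure only | 0.49 | 33.2% |
| 50% | No residual, T0 and exposure | 0.65 / 0.59 / 0.55 | 19.9 / 25.1 / 27.8% |
| 50% | Same, missing at random, correlation 0.5 | 0.58 | 26.1% |
| 50% | Residual added, exposure only | 0.63 | 21.8% |
| 50% | Residual added, T0 and exposure | 0.73 / 0.68 / 0.66 | 15.4 / 18.7 / 18.2% |
| 30% | No residual, T0 and exposure | 0.77 / 0.77 / 0.74 | 12.0 / 12.8 / 14.9% |
| 30% | Residual added, exposure only | 0.77 | 13.3% |
| 30% | Residual added, T0 and exposure | 0.80 / 0.81 / 0.78 | 11.5 / 11.3 / 12.5% |
| 50% | Multiple imputation, 20 sets | 1.02 / 0.99 / 0.98 | 4.4 / 5.0 / 5.3% |
| 50% | Complete cases | 0.98 / 0.97 / 0.98 | 5.3 / 5.3 / 5.3% |

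Understatement is one minus the ratio. At 50% dropout it runs from 1 − 0.73 = 27% to 1 − 0.49 = 51%. At 30% it runs from 1 − 0.81 = 19% to 1 − 0.70 = 30%. Under missing-at-random dropout (50%, correlation 0.5), multiple imputation gave 0.98 and 5.2%, and complete cases 0.96 and 5.7%.

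**Inflation of r.** Assume unit variances, outcomes missing at random positions, and imputation without residual from the exposure. The covariance stays at 0.30 and the outcome variance becomes (1−d) + d × 0.09.
- d = 0.5: 0.30 / √0.545 = 0.41.
- d = 0.3: 0.30 / √0.727 = 0.35.

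**The case against.** The strongest reply is that the article never says dropouts' T1 scores will be imputed. The rule sits in a paragraph on categorical sociodemographic variables, and recruiting 300 to retain 149 is how one plans when dropouts leave the analysis. This stands in part: application to the primary outcomes is implied, not stated. But the rule refers to missing data without restriction, its distinction between missingness mechanisms fits an inferential analysis, and nothing else in the article governs T1 gaps.

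Other limits also stand. The branch is conditional. That there is a single imputation, with or without a residual, is my reading of the term. The 50% is a planning ceiling. Adding a residual does not rescue the method, however: error remains 15-22% at 50% dropout.

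A reader might infer more than the article supports:
- **That the whole rule halves standard errors.** Near-halving needs the full 50% dropout and imputation without residual. Deletion does not shrink standard errors; complete-case error stayed near 5%. The weakness of deletion is possible bias when dropout depends on severity, which was not quantified here.
- **That every correlation and path is invalid.** Family history, CTQ-28, FAD-12 and all the named mediators are measured at T0. The exposure-to-mediator path and any T0-T0 correlation are untouched by T1 dropout.
- **That listwise deletion must fall below 149.** At 50% dropout, 150 completers remain, a margin of one. A larger shortfall requires an assumed missing rate per instrument and a model using all instruments at once; the article states neither.

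**Conclusion.** The point holds for the missing-at-random branch, on the condition that T1 outcomes are imputed and analysed as observed. Standard errors for quantities involving the T0-T1 change would then be too small by roughly 30-50% at the planned maximum dropout and 20-30% at about 30% dropout. Type I error would be about 15-33% and 11-17%, so at least double the nominal level throughout. Imputation without residual from the exposure would also lift an r of 0.30 to about 0.41 at 50% missing.

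The sizes depend on the assumed T0-T1 correlations and were obtained for an exposure's effect on the outcome, not for a full indirect effect. In a mediation model the problem enters through the mediator-to-change and direct paths.

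**What to change.** In the missing-at-random branch, replace regression imputation of the two change outcomes with multiple imputation pooled by Rubin's rules, or with full-information maximum likelihood. Use T0 HONOSCA-SR and WHOQOL-BREF scores, T0 symptom scales, recruitment group and site as predictors. T1 care status should not be used: it is collected at T1, so dropouts will lack it. State explicitly that the rule covers the T1 primary outcomes, and report complete-case results as a sensitivity analysis.

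The cost is analysis-plan wording, some computing time, and intervals that are wider because they reflect the data actually lost. No change to recruitment or assessments is needed.

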### Data Analysis and Sample Size

Regarding our conceptual model, earlier illustrated in Figure 2, genetic vulnerability and environmental factors (independent variables), will be, respectively, assessed by self-reported psychiatric family history and both CTQ-28 and FAD-12 questionnaires. Firstly, we expect that youth's psychopathology during the transition period, assessed by YSR/11–18 internalizing and externalizing subscales, GHQ-12, BDI-II, BSS and BIS-11, will play a role as a mediator between previously described independent variables and change in quality of life and mental health care need between T0 and T1 (dependent variables). Thus, these variables over the transition period, evaluated by HONOSCA-SR and WHOQOL-BREF, will allow to define distinct trajectories. Secondly, dimensional aspects will be analyzed as moderating factors, representing protective or risk factors in this process. The evaluated dimensional aspects are intellectual and executive functions (WAIS-IV, TAP 2.3.1, Stroop Task, TOL, BRIEF-SR, BCIS), emotional regulation (ERQ-CA), social adaptation (SASS) and quality of care (HAQ-CP).

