**Methods and Analysis:**
*Transition_psy* is a multicenter prospective longitudinal cohort study. The transversal and trans-diagnostic approach consists of a dimensional evaluation: 300 youth at the age of 17 will be included in a cohort of in-patients, out-patients and control group. Participants will be assessed at baseline (T0) and 24 months later (T1). The primary objective to determine changes in self-rated Health Of The Nation Outcome Scales For Children And Adolescents (HONOSCA-SR) and WHO Quality of Life-BREF (WHOQOL-BREF) scores between T0 and T1. Pearson correlation and mediation analysis will be performed. A secondary objective analysis using mediation and moderation models with several dimensional aspects, including self-reported and cognitive measures, will be conducted to disentangle the potential relationships between the two scores.

**Discussion:** Transition from CAMHS to AMHS occurs at a crucial age in terms of the continuum between adolescent and adulthood psychopathology. This collaborative and cohesive protocol between CAMHS and AMHS represents the first national cohort study about Transition Psychiatry in French-speaking Belgium.

**Ethics and Dissemination:** The study protocol was approved by the Institutional Review Boards (IRB) of the three participating sites. Results will be published in peer-reviewed journals and disseminated at national and international conferences. This trial was registered in ClinicalTrials.gov (Identifier: NCT04333797) on 3 April 2020.

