### Study Setting

Recruitment settings will be clinical and non-clinical. Thus, participants will be recruited among both help-seeking or diagnosed youth and non-help-seeking participants, that represents control and possibly at-risk participants.

Clinical settings will consist in both outpatient and inpatient facilities within the urban area of Brussels, Belgium. Participants will be recruited from three general hospitals (Queens Fabiola Children's University Hospital [HUDERF], Brugmann University Hospital [CHU Brugmann] and Erasmus Hospital [CUB Erasme]), and one fully outpatients clinic (Mental Health Service at ULB [SSM-ULB]).

Participants from non-clinical settings will be recruited from the general population and from Youth Aid Residential Services (YRS) in the urban area of Brussels.

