**Secondary Outcomes**			
General questionnaire	X	X	SR^a^	Sociodemographic/Personal and family medical history^c^
Barratt impulsiveness scale version 11 (BIS-11) (20)	X		SR^a^	Symptoms/Behavior^c^
Beck cognitive insight scale (BCIS) (21)	X		SR^a^	Insight^c^
Beck Depression Inventory—Ii (BDI-II) (5)	X		SR^a^	Symptoms^c^
Beck scale of suicide ideation (BSS) (22)	X		SR^a^	Symptoms^c^
Behavior rating inventory of executive function—self report (BRIEF-SR) (23)	X		SR^a^	Executive functions^c^ Cognitive systems—cognitive control^d^
Childhood trauma questionnaire−28 (CTQ-28) (24)	X		SR^a^	Trauma^c^ Negative valence systems—sustained threat^d^
Emotion regulation questionnaire for children and adolescents (ERQ-CA) (25)	X		SR^a^	Emotion regulation^c^
Family assessment device−12 (FAD-12) (9)	X		SR^a^	Family environment^c^
General health questionnaire−12 (GHQ-12) (10)	X		SR^a^	Mental health^c^
Helping alliance questionnaire for child and parents (haq-cp) (20, 25)		X	SR^a^	Therapeutic alliance^c^
Social adaptation self-evaluation scale (SASS) (11)	X	X	SR^a^	Social adaptation^c^
Stroop task (15–17)	X		NC^b^	Executive functions^c^
Test of attentional performance version 2.3.1 (TAP 2.3.1)—subtests alertness, divided attention, flexibility and working memory (26)	X		NC^b^	Executive functions^c^
Tower of london test (TOL) (18, 19)	X		NC^b^	Executive functions^c^
Transition readiness and appropriateness (TRAM) []	X		SR^a^	Transition readiness^c^
Transition related outcomes (TROM) []		X	SR^a^	Transition outcome^c^
Wechsler adult intelligence scale 4th edition (WAIS-IV) (13, 22)	X		NC^b^	IQ^c)^
Youth self report 11–18 (YSR/11–18) (12)	X		SR^a^	Symptoms/Behavior^c^

*See the main text for a description of measures*.

*Report on*:

a *Self-Report Measure*,

b *Neurocognitive Testing; Domain*:

c *General Domain*,

d *Research Domain Criteria (RDoC)*.

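### HAQ-CP is named as a moderator of the T0–T1 change but is measured only at T1 and applies only to participants with a clinician, so it cannot support a protective-factor conclusion

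*Protocol article*

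**What the plan says.** **Role.** Data Analysis and Sample Size says that "dimensional aspects will be analyzed as moderating factors, representing protective or risk factors in this process". The list of these aspects ends with "social adaptation (SASS) and quality of care (HAQ-CP"), after the cognitive measures and the emotion regulation scale. The process being moderated leads to "change in quality of life and mental health care need between T0 and T1 (dependent variables"). No restriction to participants in care is stated.

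**Timing.** Table 2 has an entry for "Helping alliance questionnaire for child and parents (haq-cp") with a mark in the T1 column only. The text describes the scale only under Follow-Up Assessment (T1): "The perception of therapeutic alliance will be tested by the child version of the Helping Alliance Questionnaire for Child and Parents (HAQ-CP"). SASS, by contrast, is marked at both visits.

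**Content.** "The overall score for the therapeutic alliance ranges from 13 to 78 with higher scores representing higher levels of therapeutic alliance". No value is defined for a participant without a clinician.

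**Who is in the cohort.** The abstract states that "300 youth at the age of 17 will be included in a cohort of in-patients, out-patients and control group". Study Setting adds that "participants will be recruited among both help-seeking or diagnosed youth and non-help-seeking participants", the latter coming from the general population and from youth residential services.

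**Missing data.** The only rules are under Descriptive Statistics: pairwise deletion first, then listwise deletion if data are judged mainly missing completely at random, or regression imputation if missing at random is more plausible.

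**The concern.** There are two separate problems.

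The first is the order of measurement. A moderator should be fixed before the change it is said to modify. HAQ-CP is scored at the visit that closes the change interval. A young person who has improved may rate the clinician better because of that improvement. An association between HAQ-CP and change would then look like a protective effect of good care when the direction is the reverse.

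The second is applicability. An alliance score exists only for someone with a therapeutic relationship to rate. In a cohort that includes non-help-seeking youth, an absent score will often mean not applicable rather than missing. The written rules do not make that distinction. The Introduction describes youth falling between child and adult services as the problem that motivates the study, and those are among the participants likely to lack a score.

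At stake is a clinical message, that good alliance protects during transition, which this analysis could produce without being able to support it.

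**Working it through.** **1. Timing, from the passages side by side**

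- Dependent variable: score at T1 minus score at T0, for HONOSCA-SR and for WHOQOL-BREF.
- Moderator: HAQ-CP at T1, with no T0 value.
- The moderator and the endpoint of the change are therefore observed at the same visit. Alliance affecting change and change affecting alliance both predict the same association, and no earlier HAQ-CP score exists to tell them apart. This holds whatever the group sizes.

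**2. What the written rules would do to an absent HAQ-CP score**

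The secondary objective first screens risk and protective factors by linear regression, then runs mediation/moderation models. If HAQ-CP enters with the other factors:

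- Listwise deletion restricts the whole model, including the coefficients of the other factors, to those with an alliance score.
- Pairwise deletion bases the HAQ-CP terms on that subset and the remaining terms on a wider group.
- Regression imputation fills in a predicted alliance score for people who have no alliance to rate.

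**3. The plan's own sample-size figures**

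- Inputs (Data Analysis and Sample Size): r = 0.3, two-sided 5%, power 80% (the text gives this as the β-error), 84 for Pearson correlation, 149 for mediation, 300 recruited to allow half to drop out.
- Pearson, by Fisher's z: n = ((1.960 + 0.842)/atanh(0.3))² + 3 = 84.9, rounded up to 85. This agrees with 84 to within one participant.
- Dropout: 149/(1 − 0.5) = 298, in line with 300.
- At the planned allowance, 300 × 0.5 = 150 completers remain against 149 required for mediation. No margin was set aside for participants to whom a scale does not apply.
- The 149 could not be confirmed, because its effect-size metric and number of predictors are not stated. Nothing below depends on it.

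**4. How many would have a meaningful HAQ-CP score**

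Formula: n = 300 × retention × share of completers with care contact. The documents give neither the clinical/control split nor the share in care, so the share is an assumption.

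| Retention | Share 1/3 | Share 1/2 | Share 2/3 |
|---|---|---|---|
| 50% (planned allowance) | 50 | 75 | 100 |
| 70% (Attrition Bias cites rates above this) | 70 | 105 | 140 |

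**5. What a subset of that size could show**

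For a simple correlation of r = 0.3, two-sided 5%, power = Φ(atanh(0.3) × √(n − 3) − 1.960):

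- n = 50: Φ(0.3095 × 6.856 − 1.960) = Φ(0.162), about 56%.
- n = 100: Φ(0.3095 × 9.849 − 1.960) = Φ(1.088), about 86%.

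These figures are for a plain association. The article states no sample size for moderation.

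**The case against.** The strongest reply is that the article maps domains to instruments in one sentence and does not say that HAQ-CP is given to, or analysed in, controls. Which participants enter each secondary model is something a condensed article can leave to a fuller protocol or analysis plan. The missing-data rules stand beside the descriptive treatment of sociodemographic variables, and imputation is conditional. Psychiatric follow-up between T0 and T1 is recorded at T1, so youth with care contact can be identified.

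Much of this stands. A reader might infer that the plan commits to HAQ-CP in the whole cohort and to made-up alliance scores. The text does not say so: both inferences rest on the absence of a restriction, and the applicability point is therefore conditional on HAQ-CP entering a joint model.

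A reader might also infer that everyone out of care at T1 lacks a valid score. The article gives no reference period or target clinician for the scale, so a participant seen between the visits might rate that relationship. Some non-help-seeking participants may also enter care.

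A third tempting inference is that the usable sample must fall below 84. That figure belongs to the primary Pearson correlation, and the table above gives results on both sides of it.

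What the reply does not answer is timing. The article itself assigns the moderator role and the T1-only schedule, and analysis-plan wording cannot create a baseline score.

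**Conclusion.** The point holds in limited form. The timing fault follows directly from the article: a measure taken only at T1 cannot be interpreted as a moderator, or as a protective factor, for change that ends at T1. The applicability fault holds if HAQ-CP is screened or modelled jointly with the other factors under the only missing-data rules given.

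The size is conditional. About 50 to 100 of 150 completers would have a meaningful score, assuming 50% retention and one third to two thirds with care contact. Better retention raises this, and the document fixes neither input.

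The reach is limited to secondary analyses that contain HAQ-CP. It would be wrong to conclude that youth who fall between services are lost from the study's main results: the T0–T1 comparison of the primary outcomes, the Pearson correlations and the primary mediation analysis do not depend on HAQ-CP. The change is worth making because it is cheap and prevents a misleading clinical conclusion.

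**What to change.** - Take HAQ-CP out of the joint predictor screening and out of the cohort-wide moderator set.
- Analyse it separately, only in participants with psychiatric follow-up between T0 and T1, using the information already recorded at T1. Label the result an exploratory association, not moderation.
- Code HAQ-CP as not applicable for everyone else, never impute it, and report the number in the subset.
- State that the T0 SASS score is the moderator. SASS is collected at both visits, the article does not say which is used, and the T1 score would raise the same timing problem.

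The cost is a change of wording in the analysis plan, with no new data collection. The drawback is that the study would have no cohort-wide quality-of-care moderator. Adding HAQ-CP at T0 is not recommended: it would measure alliance before the service boundary, which is a different question; it would lengthen a baseline assessment that the article already treats as a recruitment burden; and with baseline recruitment scheduled to end in June 2021 it would cover at best part of the cohort.
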